# The iSTOPP study: Protocol for a proof-of-concept randomised clinical trial of sensory discrimination training in people with persistent neck pain

**DOI:** 10.1016/j.conctc.2021.100820

**Published:** 2021-07-14

**Keywords:** Neck pain, Chronic pain, Tactile acuity, Cortical reorganisation, Sensory training, Two-point discrimination

## Abstract

**Background:**

Neck pain can be associated with a reduction in tactile acuity that is thought to reflect disrupted sensory processing. Tactile acuity training may normalise sensory processing and improve symptoms. This proof-of-concept trial will assess the feasibility of a novel tactile acuity training method and whether this intervention improves tactile acuity in people with persistent neck pain.

**Methods:**

and analysis: In this two-arm randomised clinical proof-of-concept trial we will recruit participants with neck pain receiving usual care physiotherapy in a secondary outpatient healthcare setting. Thirty-six participants will be randomised 2:1 to receive four weeks of either tactile acuity training using the Imprint Tactile Acuity Device (iTAD) or a placebo intervention, in addition to usual care. The placebo intervention will consist of a de-activated TENS machine (iTENS) said to deliver a sub-threshold inhibitory therapy. Outcomes will be assessed at baseline, mid-treatment, and at 5-weeks and 2-months follow-up. The primary outcome tactile acuity will be evaluated using the two-point discrimination test and locognosia tests. Feasibility will be informed by recruitment and attrition rates, adherence, credibility of the interventions, treatment satisfaction and blinding. Pain intensity and anatomical spread will be analysed as secondary outcomes. The effect of iTAD training on tactile acuity will be assessed using a 2 (Group: iTAD vs. iTENS) x 4 (Time: baseline, mid-treatment, 5-week and 2-month outcome assessment) mixed ANOVA. Secondary outcomes including pain and pain spread, will be analysed with a focus on informing sample size calculations in future trials.

**Ethics and dissemination:**

Risks associated with this study are minor. Usual care is not withheld, and participants consent to random allocation of either iTAD or iTENS. Potential benefits to participants include any benefit associated with the interventions and contributing to research that may assist people with chronic pain in the future. Trial results will be disseminated via academic journals and conference presentations. The study is approved by the Human Research Ethics Committee of Griffith University (2017/128).

## Introduction

1

Tactile acuity refers to the accuracy and clearness with which we can feel touch. This ability is diminished in several persistent pain conditions [1], including chronic neck pain [2], back pain [3] and knee pain [4]. These sensory changes are thought to reflect changes in central processing that may be part of the aetiology of some persistent pain states [1]. While the substrate of impaired tactile acuity is debated [5], it appears to correspond to changes in primary somatosensory cortex (S1) function in some chronic pain conditions [6,7]. These findings suggest that cortical reorganisation is a shared mechanisms linking reduced tactile acuity to persistent pain [8], although it is not a consistent finding in all persist pain states [9,10].

The finding of tactile acuity deficits in people with persistent neck pain led to the hypothesis that training tactile acuity could improve pain. Indeed, some preliminary studies support this possibility in both neuropathic [11] and non-neuropathic^12 13^ pain conditions, although not all studies report positive effects [14]. Currently, success in reducing pain cannot be directly linked to improved tactile acuity, because tactile acuity is rarely used as an outcome variable [[11], [12], [13], [14]]. Additionally, differences in training paradigms among studies may affect tactile acuity improvements and explain differences in efficacy [14]. A further limitation in current tactile acuity training methods is that they are delivered manually by a clinician or other person over many hours, challenging its practicality [15]. This is especially relevant since previous reports suggest a substantial correlation (r = 0.66, p < 0.05) between time spent training and pain reduction [16].

To make sensory training more feasible, we developed the Imprint Tactile Acuity Device (iTAD)^1721^ that enables training to be carried out independent of a clinician or other person, either at home or in the clinic. Additionally, we designed a customised application that incorporates training parameters linked to successful perceptual learning [[18], [19], [20]]. Our latest data shows that as a test of tactile acuity, the iTAD may have less measurement error relative to the two-point discrimination threshold (TPDT) test [17,21,22]. This indicates that it may be more sensitive to detecting changes over time, such as due to treatment. Moreover, a small cohort study of tactile acuity training in a healthy population supported the possibility that it can improve tactile acuity [21].

While the iTAD has so far shown to be a practical and promising tool to test and train tactile acuity, additional information is needed to design and plan a full-scale RCT in people with chronic neck pain. Particularly, we must confirm that training with the device can improve tactile acuity while establishing the feasibility of an RCT of tactile training in a population with neck pain. Poor recruitment and high attrition rates are common in clinical trials and the substantial patient engagement and participation required may be barriers. Further, information regarding expected changes in pain outcomes are needed to inform sample size calculations.

## Methods

2

The study is approved by the Human Research Ethics Committee of Griffith University (2016/378) and is currently in registration with the Australia and New Zealand Clinical Trials Register ACTRN 379954. This protocol adheres to the SPIRIT guidelines [23].

### Design

2.1

A two-arm proof-of-concept randomised clinical trial will be conducted in people with persistent neck pain. All participants will receive usual physiotherapy care with the addition of either iTAD tactile acuity training (experimental group) or iTENS placebo (control group) (see Fig. 1).

**Fig. 1 fig1:**
[figure not shown]
Overview of the flow of participants through the iTAD pilot trial.

### Participant selection

2.2

Volunteers will be recruited from the Gold Coast University Hospital outpatient physiotherapy clinic. Participants will be considered for the study if aged 18 to 75, have had neck pain of at least 6 months duration and report an average neck pain intensity of at least 3 on a 10-point numeric pain rating scale (NRS) over the past week. Participants will be excluded on the basis of the following criteria: have a diagnosed systemic inflammatory condition (e.g. Rheumatoid Arthritis) or current orthopaedic disorder in their spinal region or upper limbs, a history of neck or head surgery, a history of shoulder surgery in the past 12 months, a history of neurological disease resulting in altered sensation in upper quadrants as indicated by hypoesthesia to touch (unable to feel Von Frey monofilament 4.56 (4.0 g)^24^), presence of neuropathic pain (DN-4 ≥ 4) [24], current self-reported psychiatric condition or psychological disorder other than mild to moderate depression or anxiety. Participants taking medications will not be excluded, however medication use will be recorded for exploratory analyses.

### Randomisation and concealment

2.3

A concealed stratified permuted block-randomized allocation approach will be employed [25], where participants are randomly allocated to the experimental or control group with a 2:1 ratio. The randomised allocation sequence will be generated using Microsoft excel by an experimenter not involved in data collection. To achieve low allocation predictability, while maintaining the allocation ratio, randomisation to group will occur in blocks of three (2:1) or six (4:2) allocations. The order of the blocks will also be randomised. Further, allocation sequences will be stratified by sex, to ensure equal proportions of males and females in each group. The allocation will be recorded on dark, non-transparent cards, and inserted into opaque envelopes that will be numbered consecutively. Envelopes will be inserted in separate boxes for each sex. After baseline testing, the experimenter will open a sealed envelope, pre-prepared by a third party, containing the participant's allocation.

### Blinding

2.4

A limited deception approach will be used to maintain participant blinding. While participants understand they will be randomised to one of two groups, one of which may be usual care plus a placebo, once the intervention phase commences the therapist will act as though participants are undergoing active interventions regardless of allocation. Additionally, participants will be blinded towards the allocation ratio. The researcher responsible for assessing outcomes will also be blind to group allocation. A questionnaire with five response categories will be used to quantify blinding of the patient and outcome assessor at the end of the study [26]. Bang's blinding index will be calculated for each treatment arm, as well as for the outcome assessor to estimate blinding success [26]. Patients will also be asked to complete the Credibility Scale to establish the degree to which the iTAD and iTENS interventions were perceived as legitimate [27]. The Credibility Scale will be completed verbally over the phone three days into the intervention.

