### Sample size

2.5

Previous single-armed trials investigating (manual) tactile training for patients with chronic pain found moderate to large effect sizes for within group change in tactile acuity (26% improvement, mean change: TPDT 17.1 mm, p < 0.01, Cohen's d = 1.06) [28] and pain intensity (22% improvement, mean change: VAS 1.0 cm, p = 0.02, Cohen's d = 0.55) [16]. We therefore expect that we need to reach at least medium-large effects in tactile acuity in order to mediate clinically meaningful changes in pain. However, these effect sizes are based on within-group change since a control group was not present. Nevertheless, similar size differences in change of pain intensity have been reported when comparing tactile acuity training to a control condition for: neck pain [29] (24% difference, Δ NRS 1.6 points, p = 0.02, Cohen's d = 0.44); back pain [29] (41% difference, mean change: NRS 2.3 points, p < 0.01, Cohen's d = 1.07); and phantom limb pain [30] (45% improvement, mean change: Multidimensional Pain Inventory 1.5 points, p = 0.02, Cohen's d = 1.16). However, since these studies did not include tactile acuity as an outcome measure, they are not directly informative for our primary research question. As such, a sample size calculation was performed to account for a >90% chance of finding a statistically significant (p < 0.05), medium-large ($\eta_{p}^{2}$ = 0.1) between-group difference in tactile acuity, using a within-between repeated-measures ANOVA with four time-points. The calculation estimated that 18 participants would be required. Accounting for a dropout rate which can be up to 20% for treatments involving active participation in people with health conditions [31,32] a pool of 24 participants (12 in each arm) were estimated to be necessary. To improve power to explore secondary outcomes, particularly within the tactile training group, the target sample size for the intervention arm was doubled (n = 24 intervention group; n = 12 control group).

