### Primary outcome measures

2.10

Tactile acuity measures will be assessed prior to the intervention (baseline), and at mid-treatment, 5-week follow-up (i.e., within 1-week of treatment completion and 5-weeks after commencement), and 2-month follow-up (i.e., 2-months after commencement) (See Table 1). Data relating to feasibility will be collected throughout the study.

**Table 1 tbl1:** Outcomes measures.

	Domain	Measures	Timepoints
Primary outcomes	Tactile acuity	Two-point discrimination Locognosia	1,2,3,4
			1,2,3,4
	Feasibility	Recruitment rates, adherence (training duration), dropouts Bang's Blinding Index Perceived treatment credibility (Credibility Scale)	Throughout
			4
			*1
Secondary outcomes	Pain Intensity	Pain intensity: 0–10 NRS current, average & worst pain in the past week	1,2,3,4
	Pain spread	Self-indicted on body chart	1,2,3,4
	Tactile acuity	iTAD overall score	1,2,3,4
Exploratory outcomes	Perceived change	Global Perceived Effect (GPE)	2,3,4
	Disability	Neck Disability Index	1,2,3,4
	Tactile acuity	iTAD sub-scores	1,2,3,4
Exploratory predictors	Training hours	Training log	4
	Sleep	Insomnia Severity Index	3
	Psychological	Depression Anxiety & Stress Scale	1
	Baseline measures	Tactile acuity	1

*Time points: 1 = baseline, *1 = three days into the intervention, 2 = mid-treatment, 3 = 5-week outcome assessment (within 1-week of intervention completion), 4 = 2-month outcome assessment.

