***Feasibility:*** Feasibility, with respect to planning a full-scale RCT, will be assessed according to recommended a framework [34]. Data to assess feasibility will be extracted from a digital record of recruitment and screening-related interactions, iTAD digital usage logs, participant completion rates, and questionnaires related to blinding, treatment credibility, and treatment satisfaction. For the protocol to be classified as feasible, a priori cut offs have been determined. These include: 1. A minimum intake of two participants per week and a positive recruitment rate of at least one participant intake out of every four invited, 2. An 80% treatment completion rate, 3. A follow-up rate of 70%, 4. A maximum of 10% missing data for primary and secondary outcomes for those that completed the study, 5. Adherence rates where at least two-thirds of participants complete over 50% of the prescribed training, 6. No statistically significant difference in credibility between intervention and control, a 7. Bangs blinding index of 0 ± 0.2 for both treatment arms as well as the outcome assessor (on a −1 to 1 scale, where scores closer to 0 represents being more unsure of group) [[35], [36], [37]], and 8. Neutral positive satisfaction with treatment ratings for both treatment arms.

***Adverse events:*** For the purpose of this trial, a serious adverse event is defined as an unwanted and harmful outcome that: 1. be related to the intervention, and 2. is significant enough to require medical attention. A minor adverse event will be defined as any unwanted outcome that: 1. either interferes with activities of daily living or persists for more for 24 h, and 2. can be related to the intervention. Adverse events will be monitored during the weekly phone calls with the study clinician.

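### The allocation guess behind Bang's index is taken only at 2 months, so the blinding criterion describes completers and leaves out anyone who withdrew earlier

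*Protocol article*

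**What the plan says.** Section 2.4 (Blinding) sets a single occasion for the allocation guess: "A questionnaire with five response categories will be used to quantify blinding of the patient and outcome assessor at the end of the study". Table 1 in section 2.10 matches it. The feasibility row lists "Recruitment rates, adherence (training duration), dropouts Bang's Blinding Index Perceived treatment credibility (Credibility Scale" against three timings in turn: throughout, time point 4, and three days into the intervention. Bang's index therefore falls at time point 4, which the footnote defines as "4 = 2-month outcome assessment". Treatment lasts four weeks and the 2-month visit is counted from commencement, so the guess comes about four weeks after device use ends. No guess is assigned to the mid-treatment visit, the weekly contacts, the 5-week visit or withdrawal.

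The feasibility paragraph of section 2.10 makes the index a criterion for calling the protocol feasible (criterion 7): "Bangs blinding index of 0 ± 0.2 for both treatment arms as well as the outcome assessor". Criterion 3 in the same list is "A follow-up rate of 70" per cent. Section 2.5 plans for loss as follows: "Accounting for a dropout rate which can be up to 20% for treatments involving active participation in people with health conditions". The arm sizes are "n = 24 intervention group; n = 12 control group".

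**The concern.** Criterion 7 helps decide whether this placebo can be carried into a full-scale trial. The people best placed to show that it fails are those who were not convinced by it. The control unit delivers no current and is to be used for an hour a day, five days a week (section 2.8). A participant who concludes that it is inert has a reason to leave. If some do, they are absent when the question is asked, and the index among those who remain is closer to zero than it would be over everyone randomised.

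Section 2.4 and Table 1 agree on the timing, so the article itself fixes this choice. At stake is a feasibility decision that passes the blinding criterion on a selected group, in an arm small enough for two or three people to move the result.

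**Working it through.** **Inputs.** Control arm n = 12 and iTAD arm n = 24 (section 2.5). Limits ±0.2 per arm (section 2.10, criterion 7). Planned dropout up to 20% (section 2.5). Follow-up criterion 70% and treatment completion criterion 80% (section 2.10, criteria 3 and 2). Assumed, because the documents do not give them: the completers' index c, the number of leavers k, and the leavers' own index b, where b = 1 means all are certain and correct.

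**The plan's own figures.** The plan gives no figure for how attrition affects the index. Its dropout allowance does reproduce: 18 participants is 9 per arm, 9/0.8 = 11.25, rounded up to 12 per arm, or 24 in total. The intervention arm was then doubled, and the control arm stayed at 12.

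**How many controls could be lost.**
- At the planned 20%: 0.20 × 12 = 2.4, so about 2.
- Criterion 3 read per arm: losing 3 leaves 9/12 = 75%, which passes. Losing 4 leaves 8/12 = 66.7%, which fails.
- Criterion 3 read over the whole trial: 0.70 × 36 = 25.2, so 26 must be followed and up to 10 may be lost. Four of those could be controls.

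The protocol does not say which reading of criterion 3 applies.

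**Index over everyone randomised to control.** Bang's index is an average over respondents, so

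index over all = [(n − k)·c + k·b] / n, with n = 12.

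| Leavers k | c = 0, b = 1 | c = 0, b = 0.5 | c = 0.2, b = 1 |
|---|---|---|---|
| 2 | 2/12 = 0.17 | 1/12 = 0.08 | (2.0 + 2)/12 = 0.33 |
| 3 | 3/12 = 0.25 | 1.5/12 = 0.13 | (1.8 + 3)/12 = 0.40 |
| 4 | 4/12 = 0.33 | 2/12 = 0.17 | (1.6 + 4)/12 = 0.47 |

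In the first two columns the 2-month index would be reported as 0.00. In the third it would be reported as 0.20, just inside the limit.

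**What a breach requires.** With c = 0, the index over all exceeds 0.2 when b > 0.2 × 12/k. That is b > 0.8 for 3 leavers and b > 0.6 for 4. For 2 leavers it would need b > 1.2, which is impossible. Two certain leavers breach the limit only if completers are already above zero: (10c + 2)/12 > 0.2 gives c > 0.04.

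**If leavers are never asked.** Setting b to −1 and +1 bounds the result. With c = 0 and 3 leavers, the index over all lies anywhere from −0.25 to +0.25, so the data could not settle criterion 7 for everyone randomised.

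**The case against.** Several points weigh on the other side.

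- **There is an early check.** The Credibility Scale is given by phone three days in, and criterion 6 compares it between arms. It reaches people who later leave. It rates perceived legitimacy, though, and does not ask for a guess. It also comes before most of the four weeks of use and before the false progression at mid-treatment (section 2.9). It mitigates the gap without closing it.
- **Departures are recorded.** Dropouts are logged throughout. If criterion 2 is read per arm, 3 of 12 controls leaving during treatment gives 75% completion, which fails 80%. Counts show that people left but not what they believed, and on a whole-trial reading 3 losses of 36 pass easily. Criterion 4 on missing data covers only those who completed the study.
- **The placebo was designed to be believed.** Participants are told that the therapy is sub-threshold (Abstract), so feeling nothing is expected. People with neck pain were also consulted on the control condition and the treatment explanations (section 2.15). A reader might infer that participants will see through the unit and leave for that reason. The documents do not say so. Stopping the device is also not leaving the study: a non-user can still answer at 2 months.
- **Completers are a relevant group.** For bias in the 2-month outcome, those who supply that outcome are the people whose beliefs matter. This stands, and it is why the completers' index should still be reported.
- **A late question avoids prompting.** Asking everyone at week 4 or 5 would invite thoughts about allocation before the 2-month tactile acuity assessment. This also stands, and it argues against moving the main guess.

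A reader might extend the point to treatment satisfaction, since criterion 8 reads "8. Neutral positive satisfaction with treatment ratings for both treatment arms" and Table 1 gives it no time point. The article does not say when satisfaction is asked, and a condensed article may leave that to the full protocol, so selection there cannot be shown.

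**Conclusion.** The point holds in a limited form. The protocol takes the guess once, at 2 months, so criterion 7 is judged on completers, and neither the day-3 Credibility Scale nor the dropout counts supply the missing guesses.

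Whether this distorts the result depends on an assumption that the documents neither make nor exclude: that leaving is related to unmasking. From completers at 0.00, a breach needs at least 3 of the 12 controls to leave with an index above 0.8, or 4 with an index above 0.6. At the planned 20% loss (2 controls) the index reaches at most 0.17. Less is needed if completers already sit above zero. The stronger conclusion, that the placebo will look well blinded because the unconvinced have gone, is not supported. What is supported is that the design as written could not detect this if it happened.

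**What to change.** Keep the 2-month guess for everyone who stays. Amend Table 1 so that anyone who withdraws before 2 months is given the same five-category item at exit. It should preferably be self-completed, or asked by someone other than the study clinician: section 3.2 says the therapist is not blinded, and under section 2.4 the therapist acts as though both interventions are active.

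Report Bang's index for each arm in two ways: for completers, and for all randomised participants with a response. Add bounds for those who give none, and state in advance that criterion 7 is judged on the version that includes leavers.

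The cost is one short item for the few who leave and an amended table row. The guesses will have been made at different times, and some leavers will not respond, which is why the bounds are needed. Participants who stay are not prompted any earlier than now planned.

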### Sample size

2.5

Previous single-armed trials investigating (manual) tactile training for patients with chronic pain found moderate to large effect sizes for within group change in tactile acuity (26% improvement, mean change: TPDT 17.1 mm, p < 0.01, Cohen's d = 1.06) [28] and pain intensity (22% improvement, mean change: VAS 1.0 cm, p = 0.02, Cohen's d = 0.55) [16]. We therefore expect that we need to reach at least medium-large effects in tactile acuity in order to mediate clinically meaningful changes in pain. However, these effect sizes are based on within-group change since a control group was not present. Nevertheless, similar size differences in change of pain intensity have been reported when comparing tactile acuity training to a control condition for: neck pain [29] (24% difference, Δ NRS 1.6 points, p = 0.02, Cohen's d = 0.44); back pain [29] (41% difference, mean change: NRS 2.3 points, p < 0.01, Cohen's d = 1.07); and phantom limb pain [30] (45% improvement, mean change: Multidimensional Pain Inventory 1.5 points, p = 0.02, Cohen's d = 1.16). However, since these studies did not include tactile acuity as an outcome measure, they are not directly informative for our primary research question. As such, a sample size calculation was performed to account for a >90% chance of finding a statistically significant (p < 0.05), medium-large ($\eta_{p}^{2}$ = 0.1) between-group difference in tactile acuity, using a within-between repeated-measures ANOVA with four time-points. The calculation estimated that 18 participants would be required. Accounting for a dropout rate which can be up to 20% for treatments involving active participation in people with health conditions [31,32] a pool of 24 participants (12 in each arm) were estimated to be necessary. To improve power to explore secondary outcomes, particularly within the tactile training group, the target sample size for the intervention arm was doubled (n = 24 intervention group; n = 12 control group).

